# Association between preoperative evaluation with lung ultrasound and outcome in frail elderly patients undergoing orthopedic surgery for hip fractures: study protocol for an Italian multicenter observational prospective study (LUSHIP)

**DOI:** 10.1186/s13089-021-00230-w

**Published:** 2021-06-07

## Abstract

**Background:**

Hip fracture is one of the most common orthopedic causes of hospital admission in frail elderly patients. Hip fracture fixation in this class of patients is considered a high-risk procedure. Preoperative physical examination, plasma natriuretic peptide levels (BNP, Pro-BNP), and cardiovascular scoring systems (ASA-PS, RCRI, NSQIP-MICA) have all been demonstrated to underestimate the risk of postoperative complications. We designed a prospective multicenter observational study to assess whether preoperative lung ultrasound examination can predict better postoperative events thanks to the additional information they provide in the form of “indirect” and “direct” cardiac and pulmonary lung ultrasound signs.

**Methods:**

LUSHIP is an Italian multicenter prospective observational study. Patients will be recruited on a nation-wide scale in the 12 participating centers. Patients aged  >  65 years undergoing spinal anesthesia for hip fracture fixation will be enrolled. A lung ultrasound score (LUS) will be generated based on the examination of six areas of each lung and ascribing to each area one of the four recognized aeration patterns—each of which is assigned a subscore of 0, 1, 2, or 3. Thus, the total score will have the potential to range from a minimum of 0 to a maximum of 36. The association between 30-day postoperative complications of cardiac and/or pulmonary origin and the overall mortality will be studied. Considering the fact that cardiac complications in patients undergoing hip surgery occur in approx. 30% of cases, to achieve 80% statistical power, we will need a sample size of 877 patients considering a relative risk of 1.5.

**Conclusions:**

Lung ultrasound (LU), as a tool within the anesthesiologist’s armamentarium, is becoming increasingly widespread, and its use in the preoperative setting is also starting to become more common. Should the study demonstrate the ability of LU to predict postoperative cardiac and pulmonary complications in hip fracture patients, a randomized clinical trial will be designed with the scope of improving patient outcome.

*Trial registration *ClinicalTrials.gov, NCT04074876. Registered on August 30, 2019.

**Supplementary Information:**

The online version contains supplementary material available at 10.1186/s13089-021-00230-w.

## Background

One of the most common orthopedic causes leading to hospital admission in frail elderly patients is hip fracture [1, 2]. According to the European Society of Cardiology (ESC) and the European Society of Anesthesiology (ESA) guidelines, hip surgery is associated with an intermediate level risk of complication, ranging between 1 and 5% [3, 4]. However, in elderly patients with limited physiological reserve, the incidence of complication is much higher, between 22 and 53%; thus hip fracture fixation should be considered a high-risk procedure in these patients [5]. Anesthesiologists are expected to assess the risk of these patients and to take the necessary steps to improve their outcome [6, 7]. Today, to quantify and predict the risk of perioperative morbidity and mortality in these patients, in particular of cardiac origin, the following classification systems are frequently used: the American Society of Anesthesiologists Physical Status (ASA-PS) [8] the revised cardiac risk index (RCRI) [9], and the National Surgical Quality Improvement Program Myocardial infarction and Cardiac Arrest (NSQIP-MICA) [10]. Unfortunately, the literature shows that these scores generally work only moderately well and do not accurately predict mortality risk [11]. The ESC/ESA and the American College of Cardiology and American Heart Association (ACC/AHA) guidelines recommend the evaluation of metabolic equivalents (METS) as an important tool for patient risk stratification [3, 4, 12]. But METS evaluation in older patients with many comorbidities is not feasible. Indeed, studies confirming the utility of METS, both self-reported and tested, in these patients are still lacking [13, 14]. The Canadian Cardiovascular Society guidelines for perioperative cardiac risk assessment and management in noncardiac surgery patients have included the use of natriuretic peptide assessment (brain natriuretic peptide [BNP] and its precursor pro-natriuretic peptide NT-pro-BNP natriuretic peptide) in their centripetal key decision tree model [15]. But, once again, in moderate and higher risk patients, the use of these screening tools has shown a high negative predictive value (NPV), whilst performing better in relation to low-risk patients [16, 17].

Lung ultrasound (LU) has become an indispensable tool within the Anesthesiologist’s diagnostic arsenal, and some reports have started to highlight its role in the perioperative setting for perioperative outcome evaluation [18–20]. It is, therefore, fundamental that the utility of this tool be investigated in a large patient population in much greater detail. Considering the fact that LU examination is based on the exploration of ultrasound artifacts (A-lines, B-lines, lung sliding, focal interstitial syndrome—i.e., multiple B-lines) and the consolidated parenchyma, as well as pleural effusion in patients with pneumonia [21], we hypothesize that this tool may provide better “direct” evidence of preoperative pulmonary status—also supported by the fact that the sensitivity and specificity of LU are both known to be superior to chest radiography, which provides relevant information in just 0.1% of cases [22]. Furthermore, through the detection of diffuse B-lines over different zones, LU permits us to make an “indirect” evaluation of the underlying cardiac status of patients suffering from cardiac disease [23, 24]. Both these characteristics of LU could also echo the American College of Physicians (ACP) recommendation that all patients with hip fracture should undergo a risk assessment that focuses on chronic obstructive pulmonary disease (COPD) and congestive heart failure [25]. The primary aim of the present study is to evaluate, in a large population of elderly patients undergoing hip fracture repair, whether a systematic preoperative LU examination is able to provide bedside real-time information pertaining to the patients’ underlying “indirect” cardiac and “direct” pulmonary statuses, and can be used to asses perioperative cardiac and pulmonary outcome. The second aim is to compare the data gathered in the form of the lung ultrasound score (LUS) with the data provided by the traditional risk scores for preoperative evaluation, i.e., by ASA-PS, RCRI, NSQIP-MICA.

## Methods

This study was approved by the Ethics Committee of Friuli Venezia Giulia (CEUR-FVG), being the coordinating center, with the identification number 2817, dated June 4, 2019. The study was also registered at clinicaltrials.gov (https://clinicaltrials.gov/ct2/show/NCT04074876), identifier: NCT04074876, dated August 30, 2019.

### Study design and patients

LUSHIP is an Italian multicenter prospective observational study (LUSHIP.it). Patients will be recruited on a nation-wide scale in the 12 participating centers, each of which received approval from their Institution’s Ethics Committee prior to the enrolment of the first patient. Inclusion criteria are: age  >  65 years; hip fracture needing urgent surgery (<  24 h); spinal anesthesia; informed patient consent to participate in the study. Exclusion criteria are: inability to obtain informed patient consent; acute heart failure at the time of preoperative evaluation, defined as a clinical syndrome characterized by typical symptoms: “breathlessness, ankle swelling, and fatigue, that may be accompanied by the following signs: elevated jugular venous pressure, pulmonary crackles and peripheral oedema, caused by a structural and/or functional cardiac abnormality, resulting in reduced cardiac output and/or elevated intracardiac pressures at rest or during stress” (2016 ESC Guidelines) [26]; recent major adverse cardiac events (MACE) defined as arrhythmia (atrial fibrillation/flutter), myocardial infarction, or cardiac arrest in the previous 6 months; a history of pre-existing pulmonary pathologies: known history of pulmonary fibrosis, chronic renal failure on dialysis, fibrothorax, recent pneumothorax, lobectomy or pneumonectomy.

### Protocol for lung ultrasound

The LUS recognizes four aeration patterns, and assigns to each of them a value ranging between 0 and 3. This evaluation is repeated in six areas of each lung. Using the anterior and posterior axillary line as vertical boundaries, the areas are divided into two anterior (superior and inferior), two lateral, and two posterior areas. The possible patterns are: (i) normal aeration—A-lines or less than two B-lines with lung sliding (score 0); (ii) moderate loss of aeration—three or more well-spaced B-lines with lung sliding (score 1); (iii) severe loss of aeration—coalescent B-lines with lung sliding (score 2); (iv) complete loss of aeration—tissue-like pattern or consolidation (score 3). The sum of all subscores will constitute the overall score. All adjacent intercostal spaces will be analyzed for each area by moving the probe through each space (Fig. 1) and diagram flow (Fig. 2). To standardize the evaluation of LU images, one of the authors ([name]) will coordinate the sharing by e-email of inter-reader agreement video-clip exams between the 12 centers, and the principal investigator for each Institution, plus two collaborators for each center. The ultrasound machine used in the primary center will be the GE Health-Care V-scan, but other machines available in each center could be used. Data collection will continue perioperatively and until hospital discharge for assessment of 30-day clinical deterioration, i.e., pulmonary, MACE, and mortality, defined according to the standards for definitions and use of outcome measures for clinical effectiveness research in perioperative medicine by the European Society of Anesthesia (ESA) and European Society of Intensive Care Medicine (ESICM) [27].

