### Statistical analysis

Continuous normally distributed variables will be presented as means  ±  standard deviations (SD) and compared using the Student’s *t* test. Normality will be assessed using the Shapiro–Wilk test and visual inspection of quantile–quantile plots. Non-normally distributed data will be presented as medians, 1st and 3rd quartiles, and compared using the Wilcoxon rank-sum test. Categorical data will be compared between groups using the *χ*^2^ test, or Fisher’s exact test. Possible correlations between the patient outcomes and changes in LUS score will be examined using the Spearman's rank correlation coefficient. Receiver operating characteristic (ROC) curve analysis will be used to determine optimal cut-off values of LUS score for 30-day clinical deterioration (pulmonary, major cardiovascular events) and mortality. Youden’s index calculation will define the best cut-off value. Cox proportional-hazards models for mortality or clinical deterioration as endpoints allows for the calculation of hazard ratios (HR) of baseline LUS parameters. *P *values less than 0.05 will be considered to indicate statistical significance. Statistical analysis will be performed using the R environment (R Foundation for Statistical Computing, Vienna, Austria) and the appropriate packages.

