### Power analysis

We estimate that 40% of patients have focal or diffuse B-lines with an altered LUS score—unexposed/exposed ratio: 1.5—and that 30% of patients have no B-lines, but could run into MACE with a relative risk of 1.5 [30, 31]. Considering that the rate of MACE in patients undergoing hip surgery is about 30%, we calculated a relative risk of 1.5. Therefore, we estimated that we would need a sample size of 877 patients in order to obtain 80% statistical power.

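### Data collection is stated to end at hospital discharge, but the endpoints and the ROC cut-offs are defined at 30 days; no source is described for patients discharged alive before day 30

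*Protocol article*

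**What the plan says.** The Methods section on the lung ultrasound protocol holds the only statement on follow-up: "Data collection will continue perioperatively and until hospital discharge for assessment of 30-day clinical deterioration". It lists the outcomes as pulmonary events, MACE and mortality.

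The 30-day horizon appears in two other places. The abstract's Methods paragraph says: "The association between 30-day postoperative complications of cardiac and/or pulmonary origin and the overall mortality will be studied". The Statistical analysis section applies ROC curves and Youden's index to find "optimal cut-off values of LUS score for 30-day clinical deterioration (pulmonary, major cardiovascular events) and mortality". The same section adds a time-to-event analysis: "Cox proportional-hazards models for mortality or clinical deterioration as endpoints allows for the calculation of hazard ratios (HR) of baseline LUS parameters". It gives no rule for a patient who leaves hospital alive before day 30.

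The article mentions no visit, telephone call, registry linkage or vital-status check after discharge. The limitations in the Discussion cover centre experience, ultrasound machines, differences in clinical management and the excluded patients, but not this.

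**The concern.** The endpoint has a fixed window, while the stated data source ends on a day that varies between patients and probably depends on how well they recover. For a patient discharged alive on, say, day 8, status from day 8 to day 30 is unknown.

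A ROC analysis at 30 days needs a yes or no for each patient. Counting such a patient as event-free misclassifies later events. Leaving the patient out selects on recovery. In either case the accuracy measures and the cut-off are not 30-day quantities. In the Cox model the natural handling would be censoring at discharge, which is plausibly informative because patients tend to go home when they are well.

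A second risk is unequal observation. If patients with a higher lung ultrasound score (LUS) stay longer, they are watched longer, and more of their events are recorded. Part of the association with LUS could then come from observation time. This touches the primary aim, which is whether preoperative lung ultrasound predicts cardiac and pulmonary outcome.

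**Working it through.** **1. The text.** Collection ends at discharge (lung ultrasound section). The endpoint horizon is day 30 (abstract, lung ultrasound section, Statistical analysis). The two agree only for patients who die in hospital or stay at least 30 days. For all others no source is described. The contradiction needs no arithmetic.

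**2. The plan's own figure, used as a base for power.** Inputs from Power analysis: "We estimate that 40% of patients have focal or diffuse B-lines with an altered LUS score", "unexposed/exposed ratio: 1.5", MACE about 30%, effect 1.5, 80% power. From Statistical analysis: "values less than 0.05 will be considered to indicate statistical significance", taken here as two-sided.

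- Read as a relative risk (30% vs 45%), the pooled two-proportion formula gives 135 + 203 = 338, not 877.
- Read as an odds ratio, the exposed rate is 0.45/1.15 = 0.391. The Kelsey formula is n = (1.96 + 0.84)² × p̄(1 − p̄) × (r + 1)/(r d²), with r = 1.5, p̄ = 0.3365 and d = 0.0913. It gives n = 350.4, so 351 + 526 = 877.

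That labelling is a separate matter. Here it only fixes the base: 877 assumes that all events in the window are counted. If a share f is captured equally in both groups, power at 877 on the odds-ratio base is 80% for f = 1, 66% for f = 0.8 and 51% for f = 0.6. On the stated relative-risk base it is 99%, 97% and 88%.

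**3. How many 30-day events fall before discharge?** The article gives no length of stay, no event timing and no relation between LUS and stay. Everything in this step is therefore assumed: 30% true event rate by day 30 in both groups (no LUS effect) and gamma-distributed stay with shape 4. Let θ = mean stay/4.

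- Front-loaded events with exponential mean m days: captured share ≈ [1 − (1 + θ/m)⁻⁴] / (1 − e^(−30/m)).
- Constant hazard λ = −ln(0.7)/30 = 0.0119 per day: captured share ≈ [1 − (1 + θλ)⁻⁴] / 0.30.

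With mean stay 10 days (θ = 2.5):
- constant hazard: (1 − 0.889)/0.30 = 0.37
- m = 8: (1 − 0.337)/0.976 = 0.68
- m = 3: (1 − 0.089)/1.000 = 0.91

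The formulas ignore stays beyond day 30. The table cuts observation at day 30 by numerical integration.

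**4. Spurious relative risk when the exposed stay 10 to 30% longer.** Replace θ by 1.1θ to 1.3θ in the exposed and divide the recorded proportions. The rejection probability is for a crude two-proportion test with 351 and 526 patients: Φ((d − 1.96 s₀)/s₁) + Φ((−d − 1.96 s₀)/s₁), where d is the difference in recorded proportions, s₀ the pooled and s₁ the unpooled standard error.

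| Assumed timing | Mean stay | Captured | Recorded RR, stay +10% to +30% | False-positive rate |
|---|---|---|---|---|
| Constant hazard | 10 d | 37% | 1.09 to 1.27 | 7.6 to 26.3% |
| Mean 8 d | 10 d | 68% | 1.05 to 1.12 | 6.4 to 14.5% |
| Mean 8 d | 20 d | 88% | 1.02 to 1.06 | 5.5 to 7.8% |
| Mean 3 d | 10 d | 91% | 1.02 to 1.04 | 5.2 to 6.4% |

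Example (constant hazard, +30%): recorded proportions 0.1401 and 0.1105, d = 0.0296, s₀ = 0.0226, s₁ = 0.0230. The first term is Φ(−0.64) = 0.26.

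These figures concern crude recorded proportions, as in a chi-square or ROC analysis that counts unobserved patients as event-free. They do not test the Cox model: stay is independent of event time within each group here, so censoring at discharge would be non-informative.

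**The case against.** The article condenses a fuller protocol. The case report form (an additional file) and the enrolment flow figure are not shown, and either could contain a day-30 contact. The sentence on follow-up is one clause in the section on ultrasound technique. The Statistical analysis section does not say that discharged patients are counted as event-free or censored at discharge, and such rules are commonly left to an analysis plan. Length of stay and event timing are assumptions, and with early events or long stays the error is small.

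Much of this stands. A reader might infer that post-discharge events are certainly lost; the documents support only that, as written, nothing describes how they would be recorded. A reader might also infer that the ROC and Cox analyses are bound to mishandle discharged patients. That is an inference about likely handling, not a stated rule.

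The objection does not remove the point. The article is not silent on follow-up: it states where collection ends, and that end conflicts with the stated window. If the case report form does contain a day-30 contact, the sentence is wrong and has to be corrected.

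**Conclusion.** The conflict between the end of data collection and the 30-day endpoints is real and rests on the text alone. Followed as written, the study would report in-hospital rates, AUC, sensitivity, specificity and cut-off under a 30-day label, with observation time that varies with length of stay.

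The size cannot be settled from the documents. Under the assumptions shown, capture of 30-day events runs from about 37% to about 91%, and the spurious relative risk from about 1.02 to 1.27, so the effect may be negligible or large. It would be tempting to conclude that an association with LUS would be an artefact, or to quote the 26% false-positive rate as the study's error rate. The documents do not support either: they do not say that patients with a high LUS stay longer, the 26% belongs to the least favourable timing tried, and informative censoring in the Cox model is plausible but has not been shown.

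**What to change.** **Preferred.** Ascertain status at day 30 for every patient, whether discharged or not: vital status, readmission, and the cardiac and pulmonary events that make up the endpoint. Use that status in the ROC analysis and censor administratively at day 30 in the Cox model. Amend the sentence on data collection to name the source. The cost is one short call or record check per patient, with no change to the sample size. The Conclusions say that enrolment is still under way, so it can be added now; for patients already past day 30 it would have to rely on records or recall.

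**Otherwise.** Rename the endpoints 'in-hospital, up to day 30', drop the 30-day claims from the abstract and the ROC and mortality statements, and state as a limitation that observation time differs with length of stay. This needs no new data, but it gives up the 30-day claim. It corrects the label without removing the unequal observation. Competing-risk modelling does not remove it either: a cause-specific Cox model with discharge alive as a competing event is the same fit as censoring at discharge, and a Fine-Gray model keeps discharged patients in the risk set, so a longer stay still raises recorded incidence.

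If the case report form or the flow figure already provides a day-30 contact, correcting the text to match is enough.

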**Fig. 1 Fig1:**
[figure not shown]
Each hemithorax is divided in six regions: two anterior, two lateral, and two posteriors, following to anatomical landmarks set by parasternal, anterior and posterior axillary lines. Each region is divided in superior and inferior. To perform an examination, adjacent intercostal spaces are explored in each region of interest, sliding the probe along intercostal space

**Fig. 2 Fig2:**
[figure not shown]
Study flow enrolment

### Patient consent and data protection

Patients will receive information about the study, and written consent will be requested. In the case that the patient is unable write their signature, verbal consent will be asked in the presence of two testimonies. Patient data will be processed according to the Declaration of Helsinki and the European Privacy Regulation 2016/679 for General Data Protection Regulation (GDPR). The implementation of the study will not alter the management of the patient in any way during or following surgery. Each center is provided with an identical case report form (CRF) (Additional file 1). A principal investigator (PI) will be nominated for each participating center, who will be responsible for their institution’s data collection, ensuring proper concealment of patient identity on the linked CRF, and storing links between sensitive data and patient univocal codes under password protection. De-identified patient data will be uploaded onto a web platform by each PI, who will be provided with a personal username and password, thereby creating the study’s final database. The steering committee will consist of four investigators ([name]) plus six members with recognized expertise in LU ([name]). In the case of any difficulties or problems, each PI will be able to communicate with the study’s other PI. Two independent investigators will perform data management activities on the database and check for abnormalities and inconsistencies. The study will be reported according to the Standards for the Reporting of Diagnostic Accuracy Studies (STARD) for Point-of-Care Ultrasound (POCUS) [28, 29]. (The STARD checklist for this diagnostic accuracy study is reported in the Additional file 2).

### Statistical analysis

Continuous normally distributed variables will be presented as means  ±  standard deviations (SD) and compared using the Student’s *t* test. Normality will be assessed using the Shapiro–Wilk test and visual inspection of quantile–quantile plots. Non-normally distributed data will be presented as medians, 1st and 3rd quartiles, and compared using the Wilcoxon rank-sum test. Categorical data will be compared between groups using the *χ*^2^ test, or Fisher’s exact test. Possible correlations between the patient outcomes and changes in LUS score will be examined using the Spearman's rank correlation coefficient. Receiver operating characteristic (ROC) curve analysis will be used to determine optimal cut-off values of LUS score for 30-day clinical deterioration (pulmonary, major cardiovascular events) and mortality. Youden’s index calculation will define the best cut-off value. Cox proportional-hazards models for mortality or clinical deterioration as endpoints allows for the calculation of hazard ratios (HR) of baseline LUS parameters. *P *values less than 0.05 will be considered to indicate statistical significance. Statistical analysis will be performed using the R environment (R Foundation for Statistical Computing, Vienna, Austria) and the appropriate packages.

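### The LUS cut-offs are chosen by Youden's index in the one study cohort with no optimism correction stated, so sensitivity and specificity read there would be overstated: slightly at 30% events, more for a rarer outcome such as mortality

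*Protocol article*

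**What the plan says.** The score sums twelve regional subscores, so that "the total score will have the potential to range from a minimum of 0 to a maximum of 36" (Abstract, Methods). In the Statistical analysis section, ROC analysis "will be used to determine optimal cut-off values of LUS score for 30-day clinical deterioration", and likewise for mortality. The selection rule is explicit: "Youden’s index calculation will define the best cut-off value".

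The same section plans Cox models, and says that this "allows for the calculation of hazard ratios (HR) of baseline LUS parameters"; it does not say that LUS will be split for them. A further sentence begins "Categorical data will be compared between groups using the" and names the chi-square or Fisher test, without defining the groups. The significance rule is that P "values less than 0.05 will be considered to indicate statistical significance".

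The Power analysis section uses a fixed exposure instead of a Youden cut-off: "We estimate that 40% of patients have focal or diffuse B-lines with an altered LUS score", with 1.5 unexposed patients per exposed patient, a relative risk of 1.5, MACE in about 30%, and 877 patients in total. The section on patient consent and data protection describes the work as a diagnostic accuracy study to be reported under STARD.

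**The concern.** A score from 0 to 36 offers up to 36 thresholds. Youden's index takes the one where sensitivity plus specificity minus 1 (J) is largest in the observed data. That maximum is partly chance, so sensitivity and specificity at the chosen cut-off look better in the patients who supplied it than they would in new patients. The search is made separately for deterioration and for mortality, and the chance part grows as events become fewer.

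In a study reported as diagnostic accuracy, these figures are natural headline results. The second aim compares LUS with ASA-PS, RCRI and NSQIP-MICA. If that comparison were made at cut-offs, a LUS threshold tuned on these patients would have an advantage over cut-offs for the older scores that were set elsewhere. A p-value computed on groups split at the tuned threshold would also lose its nominal 5% level, because the outcome would have helped to define the groups.

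**Working it through.** **Inputs from the article.** 877 patients; score 0 to 36; 40% exposed; relative risk 1.5; about 30% events (stated for MACE, used here for deterioration); 5% significance level, taken as two-sided. The sample size is taken as given. It does not follow from the stated inputs: 25% versus 37.5% at ratio 1.5, two-sided 5% and 80% power needs 445. The present point does not depend on that.

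**Assumed inputs.** The LUS distribution, in three versions: 60% at score 0 with a long tail; 60% at score 0 with a short tail; and a spread-out score that departs from the 40% exposed share. Event rates of 10% and 5% are also assumed, since the article gives no mortality rate.

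**Reference value of J under the plan's own effect.** With risk p in the unexposed and 1.5p in the exposed, the overall rate is 0.6p + 0.4 × 1.5p = 1.2p. Setting this to 30% gives p = 25%, and 37.5% in the exposed.
- Sensitivity = 0.4 × 0.375 / 0.30 = 0.50
- Specificity = 0.6 × 0.75 / 0.70 = 0.643
- J = 0.50 + 0.643 − 1 = 0.143

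**Simulation.** 40,000 cohorts of 877 per scenario. In each, the cut-off maximises J (higher LUS meaning higher risk). J is then read in the same patients (apparent) and in 877 new patients at the same cut-off.

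Relative risk 1.5 for any LUS above 0:

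| LUS distribution | Risks | Apparent J | J in new patients | Overstatement |
|---|---|---|---|---|
| 60% zero, long tail | 25% / 37.5% | 0.144 | 0.138 | 0.006 |
| 60% zero, short tail | 25% / 37.5% | 0.143 | 0.142 | 0.001 |
| Spread out | 25% / 37.5% | 0.081 | 0.059 | 0.022 |
| 60% zero, long tail | 5% / 7.5% | 0.125 | 0.083 | 0.042 |
| 60% zero, short tail | 5% / 7.5% | 0.118 | 0.086 | 0.032 |
| Spread out | 5% / 7.5% | 0.089 | 0.031 | 0.058 |

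In the lower rows the overall rate is a little above 5%: with 40% exposed it is 0.6 × 5% + 0.4 × 7.5% = 6%. When the risks are rescaled so that the overall rate is exactly 30% or 5%, the overstatement is about 0.002 to 0.025 and about 0.04 to 0.07 respectively. The first two rows also recover the hand-calculated 0.143 closely.

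No association, uncorrected chi-square test at nominal 5%:

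| LUS distribution | 30% events | 10% events | 5% events |
|---|---|---|---|
| 60% zero, long tail | 12.7% | 14.9% | 16.0% |
| 60% zero, short tail | 9.9% | 12.4% | 13.5% |
| Spread out | 15.3% | 16.5% | 17.9% |

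These are rejection rates at the same-sample Youden cut-off. Two controls locate the cause. The fixed cut LUS ≥ 1 rejects in about 5% of cohorts, and the Youden cut-off tested in new patients in about 4.5 to 5%. The excess therefore comes from choosing and testing in the same patients.

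**The case against.** The strongest reply is that the article does not describe the harmful analysis. No sentence applies a test or a Cox model to groups split at the Youden cut-off. The hazard ratios are for baseline LUS parameters, and the chi-square groups are undefined. That stands, so the 10 to 18% error rate is conditional and not a feature of the plan. The same silence bars the claim that the powered contrast is never tested, because the undefined groups could be exactly altered versus normal LUS.

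A second reply is that a journal article condenses the plan, and that bootstrap or cross-validation may be set out in a statistical analysis plan that is not shown. That also stands: one can say only that the article states no correction, not that none is planned. What remains is that the article does fix the procedure that creates the bias.

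A third reply is that the bias is trivial at the only event rate the article gives. With 60% of patients at score 0 this is right (0.001 to 0.006). The larger figures need a rarer outcome, whose rate is an assumption.

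Two further inferences fail. A reader might suppose that the cut-off will be carried into the later randomised trial; the article says only that such a trial would be designed if prediction is shown. A reader might also suppose that the AUC is inflated; it is not by this route, because LUS is a pre-defined sum and its AUC does not depend on which cut-off is picked.

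**Conclusion.** The point holds in a limited form. The cut-offs for deterioration and for mortality are chosen by Youden's index in the single cohort, and sensitivity and specificity read there in the same patients would be biased upwards. Under a relative risk of 1.5, J is overstated by about 0.002 to 0.025 at 30% events, which is minor, and by about 0.04 to 0.07 at an assumed 5% rate, which is a material share of a J near 0.1. These sizes rest on the assumed LUS distributions and, for mortality, on the assumed rate; the direction of the bias does not. The documents do not support the stronger reading that the trial's tests exceed 5%, since none is stated to use the Youden split.

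**What to change.** State that the whole cut-off selection will be bootstrapped: in each resample, choose the Youden cut-off again, compare its sensitivity and specificity there with those in the original patients, and subtract the average difference. Report the corrected sensitivity and specificity with confidence intervals, separately for deterioration and for mortality. The AUC needs no correction for cut-off selection.

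State also that p-values and hazard ratios will rest on LUS as a continuous score, or on the altered-versus-normal contrast behind the power calculation, with altered defined by the investigators before analysis, and not on the Youden split.

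The cost is a little more analysis code and slightly less favourable reported accuracy. No further patients or data are needed. The article reports that enrolment was still under way, so the wording could be settled before analysis.
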